#### 2.7.2. Aerobic Capacity

The distance covered with the 6-minute walking test (6MWT) will be evaluated to assess their aerobic capacity. The 6MWT is an easy-to-use and reliable functional capacity assessment test. It is widely used and considered ideal for patients with respiratory, cardiovascular and other diseases characterized by reduced physical fitness [44,45]. It is simple to perform, easily understood by patients and reflects patients’ ability to cope with their daily activities, which mostly require submaximal work. The distance covered during the 6-minute walking test has been found to be positively correlated with the VO_2_ peak [46].

Patients are asked to walk as far as possible for 6 min. The patient will be allowed to use an external aid. There is strong evidence for the reliability and validity of the test in patients after hip fractures. Overgaard et al. [47] reported minimum detectable changes (MDC) without aid at 59.4 m and with aid at 49.8 m. The test will be performed along a 25 m aisle, and the HR will be simultaneously recorded using a HR monitor chest strap (Polar H10, Polar Electro, Kempele, Finland). The assessment will be performed at 4, 8, 26 and 52 weeks postoperatively.

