vWF:Antigen (Ag) and vWF:Activity (Ac) are used as measures of platelet and endothelial dysfunction impacting the hemostatic equilibrium. The plasma levels of vWF:Ag and vWF:Ac will be measured using an automated latex enhanced immunoassay (HaemosIL^TM^ assay, Instrumentation Laboratory Corporation, Lexington, KY, USA) using IL (Instrumentation Laboratory) coagulation equipment (ACL TOP). The vWF:Ac will be evaluated by measuring the differences in turbidity caused by the latex reagent’s agglutination. A monoclonal anti-VWF antibody immobilized on the latex reagent interacts with the vWF in the blood sample. The agglutination is proportional to the vWF:Ac and is determined by the decreased light transmission resulting from the aggregates. The results will be presented as a percentage of the normality.

For the ROTEM analysis, within 90 min after blood collection, a citrated tube will be immediately filled with blood and will be analyzed in a ROTEM analyzer. Blood held at room temperature for up to 120 min after collection does not impact the ROTEM findings. Blood samples will be examined using a ROTEM analyzer (ROTEM delta, Tem Innovations GmbH). The ROTEM analysis includes preoperative EXTEM and INTEM testing and postoperative INTEM assays. The following EXTEM and INTEM parameters will recorded: clotting time (CT, seconds), the time from the beginning of measurement until the formation of a clot 2 mm in amplitude; clot formation time (CFT, seconds), the time from CT (amplitude of 2 mm) until a clot firmness of 20 mm was achieved; amplitude recorded at 10 min (A10, mm); an angle (a°), the angle between the central line and the tangent of the TEM tracing at the amplitude point of 2 mm describing the kinetics of clot formation; maximum clot firmness (MCF, mm), the final strength of the clot; and the lysis index at 60 min (LI60, %), which is the percentage of remaining clot stability in relation to the MCF following the 60-min observation period after CT, which indicates the speed of fibrinolysis [10].

Blood samples will be collected on the day of admission; one day before surgery; on the third postoperative day and at 1, 4, 8, 26 and 52 weeks postoperatively.

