### 2.8. Statistical Analysis

#### 2.8.1. Sample Size Calculation

Power analysis for the sample size selection to highlight the preoperative program on the change in 3-day CAS was performed via the web application http://sampsize.sourceforge.net/ (accessed on 1 June 2021) for a significance level of α = 0.05 and power = 90%. The assumptions were made based on the study by Jérôme et al. [54], where m1 = 11.2 with a standard deviation = 3.1 and m2 = 13.6 with a standard deviation of 3.1. The minimal clinically important difference (MCID) between groups for the 3-day CAS was set at 2.4 units, given that the MCID for the 1-day CAS was found to be 0.8 units [39]. The ratio between groups will be 1:1. Due to factors such as in-hospital mortality, the drop-out rate is 10%. Considering the above assumptions, the minimum required sample to highlight the preoperative effectiveness of the exercise in the immediate postoperative basic mobility assessed with the 3-day CAS is set at 80 subjects (intervention group n1 = 40, control group n2 = 40).

The power analysis for sample size selection to demonstrate postoperative program change in the 6-minute walking test after program completion at eight weeks postoperatively was also performed via the web application: http://sampsize.sourceforge.net/ (accessed on 1 June 2021), with a significance level α = 0.05 and power = 90%. Based on previous studies [47,55,56], the 6MWT after a hip fracture at various time points (6 months, 20 days and one month postoperatively, respectively) varies approximately at 250 m of travel distance with a standard deviation of between 70 and 80 m. From the above-mentioned results, our assumptions for the power analysis, also assuming a clinically significant difference between the groups at 50 m, are m1 = 250 with a standard deviation = 75 and m2 = 300 with a standard deviation of 75. Considering the ratio between groups will be 1:1, the sample size is 96 patients (48 in each group).

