However, based on the study by Karagiannis et al. [5] on a Greek population, mortality at six months after a fracture is 10.5%. However, both because this particular study reports a lower incidence of mortality at 6 and 12 months postoperatively compared to studies in other countries [57], and because of other factors that will likely contribute to the drop-out rate, such as comorbidities that will lead to the mandatory interruption of the program or the patient’s desire to interrupt the program for personal reasons, an increase in the sample size by 20% is deemed necessary, with the result that the sample size is set at 116 people (intervention group n1 = 58, control group n2 = 58).

Considering the above, in order to ensure the necessary power to investigate both primary purposes, the sample size is set at 116 subjects.

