#### 2.8.2. Data Analysis

Descriptive statistics will be used to summarize the baseline characteristics of the patients participating in each group. Continuous variables will be presented with the mean and standard deviation or median and interquartile ranges (IQR) if they do not follow a normal distribution. Categorical variables will be presented with absolute and relative frequencies (n, %). The Kolmogorov–Smirnov test will be performed to check for normality. Based on the normal or non-normal distribution of the sample, a *t*-test or Mann–Whitney test will be performed to compare the means or medians of the two groups, respectively. The chi-square test will be used to identify differences in the categorical variables between the two groups. A subgroup analysis will be performed a posteriori for the different surgical techniques used for all variables.

To detect confounding factors that may affect the functional tests (CAS, 6WMT and TUG), multiple linear regression will be performed after first performing the relevant check on whether the conditions are met to consider the linear regression results reliable. If the necessary conditions are not met, the necessary transformations of the dependent variables will be carried out.

To test the change of the parameters to be measured at multiple time points (e.g., albumin, functional score, etc.) and to compare the change between the intervention group and the control group, we will perform an analysis of variance for repeated measurements (repeated measures ANOVA).

Additionally, the time to occurrence of an event (e.g., death, readmission to hospital, thrombosis, etc.) will be presented with a Kaplan–Meier survival curve. To highlight the factors related to the time of occurrence of an event, semiparametric (Cox proportional hazard models) or parametric survival analysis models (e.g., Weibull, exponential, etc.) will be performed, as will result from the analysis that will be done.

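### Repeated-measures ANOVA of change does not test the week-8 walking difference on which the trial is sized, and it keeps only patients with every included visit

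*Protocol article*

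**What the plan says.** - **Method for repeated outcomes.** Section 2.8.2 (Data Analysis) states "we will perform an analysis of variance for repeated measurements (repeated measures ANOVA" for parameters followed over several time points, with albumin and functional score as examples. The stated aim is to compare change between the two arms.
- **Other two-group test.** The same section names a t-test or, if data are not normal, a Mann–Whitney test. It does not attach either to an outcome or a visit.
- **6MWT visits.** Section 2.7.2: "The assessment will be performed at 4, 8, 26 and 52 weeks postoperatively". Section 2.7.1 gives the same four visits for Timed Up and Go (TUG). Neither has an earlier value.
- **Treatment before the first 6MWT.** Under section 2.1 the intervention arm trains before surgery and continues straight afterwards for eight weeks.
- **Blood markers.** Section 2.7.6 lists admission, the day before surgery, and then "on the third postoperative day and at 1, 4, 8, 26 and 52 weeks postoperatively".
- **Sample size for walking.** Section 2.8.1 compares two independent means at week 8: "m1 = 250 with a standard deviation = 75 and m2 = 300 with a standard deviation of 75", "with a significance level α = 0.05 and power = 90"%, giving "Considering the ratio between groups will be 1:1, the sample size is 96 patients (48 in each group").
- **Loss.** Section 2.8.1 cites "mortality at six months after a fracture is 10.5"% and concludes that "an increase in the sample size by 20% is deemed necessary", which sets 116 patients (58 per arm).
- **Aim.** The Discussion gives the second primary purpose as the effect on walking distance at 8 weeks after surgery.

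**The concern.** The trial is sized on a difference between arms at one visit, whereas the method stated for repeated outcomes tests whether the difference changes across visits. For an outcome with an untreated baseline these are close relatives. 6MWT and TUG have none: the first value comes after the preoperative programme and about four weeks of postoperative training. Whatever the intervention has achieved by then is common to all visits, so a group-by-time test does not count it.

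The classical form of the method also needs a full row of visits per patient. Someone who walks at week 8 and then dies or misses week 52 is dropped, week-8 value included. That costs precision and tilts the result towards survivors who attend every visit, in a population where the article itself plans for substantial loss.

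At stake is the second primary question. Two tests that can disagree could both be run on 6MWT, and the text does not say which one answers it.

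**Working it through.** **1. The plan's own figure.** Inputs from section 2.8.1: difference 50 m, SD 75 m, α = 0.05 (taken as two-sided), power 90%.

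n per arm = 2 × (1.960 + 1.282)² × 75² / 50² = 2 × 10.51 × 2.25 = 47.3, so 48 per arm and 96 in total. Then 96 × 1.2 = 115.2, rounded up to 116. Both stated figures reproduce. At 48 per arm a direct week-8 comparison has 90.4% power, whatever the difference at week 4.

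**2. Patients with all four 6MWT visits.** Loss by week 52 is taken as 10.5% (the cited six-month mortality) to 20% (the planned allowance). The chance of missing any single visit is not given; 5% and 10% are assumed. Complete patients per arm = 58 × (1 − loss) × (1 − miss)⁴. Patients with a week-8 value = 58 × (1 − loss) × (1 − miss), which counts all loss as if it came before week 8 and so is conservative. Power is for a plain week-8 comparison (50 m, SD 75, normal approximation).

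| Loss | Missed per visit | Complete per arm | Power | With week-8 value | Power |
|---|---|---|---|---|---|
| 10.5% | 5% | 42.3 | 87% | 49.3 | 91% |
| 20% | 5% | 37.8 | 83% | 44.1 | 88% |
| 10.5% | 10% | 34.1 | 79% | 46.7 | 90% |
| 20% | 10% | 30.4 | 74% | 41.8 | 86% |

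Blood markers have seven planned samples after admission in the section 2.7.6 list, so the loss is larger. With 20% loss and 5% missed, 0.8 × 0.95⁷ = 0.559, or 32 of 58 per arm (admission value assumed present).

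**3. Power of the group-by-time test, with no missing data.** Assumptions: 48 complete patients per arm, four visits, SD 75 m, equal correlation ρ between visits. The article gives no ρ; 0.5, 0.7 and 0.8 are used. With d_t the arm difference at visit t and d̄ its mean, the F test has 3 and 3 × 94 = 282 degrees of freedom and noncentrality

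λ = (48/2) × Σ(d_t − d̄)² / [75² × (1 − ρ)].

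For 25, 50, 50, 50 m: d̄ = 43.75, the sum of squares is 18.75² + 3 × 6.25² = 468.75, and λ = 24 × 468.75 / [5625 × (1 − ρ)] = 2/(1 − ρ), that is 4, 6.7 and 10.

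| Difference at weeks 4, 8, 26, 52 (m) | λ × (1 − ρ) | Power, ρ = 0.5 | ρ = 0.7 | ρ = 0.8 |
|---|---|---|---|---|
| 50, 50, 50, 50 | 0 | 5% | 5% | 5% |
| 40, 50, 50, 50 | 0.32 | 9% | 12% | 16% |
| 25, 50, 50, 50 | 2 | 35.4% | 56.0% | 75.5% |
| 0, 50, 50, 50 | 8 | 93% | 99.5% | over 99.5% |

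Every row has the planned 50 m at week 8. A simulation at ρ = 0.7 (4,000 runs) gave 6%, 57% and 99.6% for the first, third and fourth rows, and 89–91% for the week-8 t-test.

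**4. Restricting the ANOVA to weeks 4 and 8.** The SD of change is 75 × √[2(1 − ρ)]. With 25 m at week 4 and 50 m at week 8, power for the difference in change is 37%, 56% and 73% at ρ = 0.5, 0.7 and 0.8. A shorter window avoids dropping patients for a missed week 52 but does not restore the early benefit.

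**The case against.** A reader might infer that group-by-time is the designated primary 6MWT test, so that the trial will miss its planned effect. The article does not support that.

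- Section 2.8.2 also names a t-test or Mann–Whitney test. Applied at week 8, that is the comparison on which the sample size rests, and it would use every available week-8 value.
- The ANOVA sentence does not name 6MWT. The section mentions CAS, 6MWT and TUG by name only under regression.
- ANOVA also yields a group main effect. For a constant 50 m at 48 per arm its power is 94–98% over ρ = 0.5–0.8; for 25, 50, 50, 50 m it is 87–95%.
- If the arms are equal at week 4, the group-by-time test loses nothing.
- The week-4 objection does not reach albumin, the other blood markers, mHHS or LEFS, which have an admission or recalled pre-fracture value.
- The article states neither listwise deletion nor which visits enter each ANOVA, and missing-data rules may properly sit in the analysis plan.

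All of this limits the point without removing it. 6MWT fits the description of a parameter measured at several time points, and nothing ties the t-test to week 8. The main effect averages weeks 4 to 52: if the benefit ran 25, 50, 25, 0 m, its power would be only 42–53% despite the same 50 m at week 8. Dropping incomplete patients is a property of the classical method that the article names, so this is not a complaint about a rule left unstated.

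**Conclusion.** The concern holds as a mismatch between the stated method and the sized question, together with inefficient use of incomplete follow-up. It does not show that the planned effect will be missed: that depends on how much benefit exists by week 4 and on which test is taken as primary.

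The size is conditional. Without missing data, group-by-time power ranges from 5% to at least 93% for the same 50 m at week 8, against 90% for a direct comparison. This rests on 48 per arm, SD 75 m, equal correlation of 0.5–0.8 between visits, and the early difference, none of which beyond the first two is given in the article. The complete-case figure of about 30–42 of 58 per arm rests on 10.5–20% loss and an assumed 5–10% missed per visit, over all four 6MWT visits. The week-4 problem applies to 6MWT and TUG; the complete-case problem applies to every repeated outcome analysed by the classical method.

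**What to change.** - State that the primary 6MWT analysis is the between-arm difference at week 8. Estimate it from a linear mixed model with arm, visit and arm-by-visit, using all available visits and without subtracting the week-4 value. Pre-fracture New Mobility Score may be added as a covariate.
- Use the same model in place of repeated-measures ANOVA for the other repeated outcomes, adjusting for the admission value where one is collected (blood markers, mHHS, LEFS).
- Report deaths by arm and add a sensitivity analysis for truncation by death. The mixed model alone does not resolve it, because a walking distance after death is not a missing value in the usual sense.

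The cost is analysis wording only: no new data, visits or patients, and standard software suffices. With the week-8 values available under the assumptions above, power for the primary contrast is about 86–91%.

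### The repeated-measures ANOVA for serial blood markers has no stated scale or sphericity handling: run uncorrected, its 5% arm-by-time test can become a 7–11% test, and the raw scale can cost power on strongly skewed markers

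*Protocol article*

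**What the plan says.** All references are to the protocol article.

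- **Method.** Section 2.8.2 introduces the longitudinal analysis with "To test the change of the parameters to be measured at multiple time points (e.g., albumin, functional score, etc" and then names the method: "we will perform an analysis of variance for repeated measurements (repeated measures ANOVA". Albumin is the only blood marker named. The haemostatic markers come in through the open-ended list, and no other longitudinal method is given for them.
- **Normality check.** "The Kolmogorov–Smirnov test will be performed to check for normality" is followed by a choice between t-test and Mann–Whitney for comparing the two groups.
- **Transformation.** This appears in the regression paragraph, which opens "To detect confounding factors that may affect the functional tests (CAS, 6WMT and TUG), multiple linear regression will be performed" and ends "If the necessary conditions are not met, the necessary transformations of the dependent variables will be carried out". No blood marker is in that regression.
- **Sampling.** Section 2.7.6 draws blood "on the day of admission; one day before surgery; on the third postoperative day and at 1, 4, 8, 26 and 52 weeks postoperatively", which is eight samples, and Section 2.7.5 gives the same schedule for albumin and prealbumin. Table 1 has no tick one day before surgery in either row, which makes seven.

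**The concern.** The uncorrected arm-by-time F test in a repeated-measures ANOVA is exact only if the difference between any two visits has the same variance (sphericity). Here some samples are days apart around trauma and surgery, and the last two are 26 weeks apart. Neighbouring samples will usually be more alike than distant ones. On the raw scale, the variance of a concentration tends to rise and fall with its level. Sphericity is therefore implausible, and the uncorrected test rejects too often.

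The second issue is scale. If a marker is strongly right-skewed and exercise changes it proportionally, a few large values dominate a raw-scale comparison. A sphericity correction does not repair that.

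At stake is the evidence on haemostasis, a secondary objective of both the preoperative and the postoperative program (Discussion) and part of the mechanism proposed under Expected Outcome. With this many markers, a scale chosen after seeing the data would also invite selective reporting.

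**Working it through.** **Inputs from the article**

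- Sample size (Section 2.8.1): n per arm = 2(z₀.₉₇₅ + z₀.₉₀)²(SD/difference)² = 2 × (1.960 + 1.282)² × (75/50)² = 47.3, so 48 per arm and 96 in all. Then 96 × 1.2 = 115.2, rounded up to 116, or 58 per arm. The stated figure reproduces. A 20% loss leaves 58 × 0.8 = 46.4, about 46 per arm.
- The article states no error rate or power for the ANOVA, so there is no further figure to reproduce.
- Samples: eight by the text, seven by Table 1.

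**Assumptions not in the article**

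- Within-patient correlation, in the patterns tabulated below.
- Admission three days before surgery.
- Log-scale SD from 0.15 to 1.0.
- Complete data.

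**The test**

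With k samples and N patients, the uncorrected F has (k−1) and (k−1)(N−2) degrees of freedom. For k = 8 and N = 116 these are 7 and 7 × 114 = 798. Departure from sphericity is measured by ε = [tr(CΣC′)]² / {(k−1) tr[(CΣC′)²]}, where Σ is the visit covariance and C holds orthonormal contrasts. ε is 1 under sphericity. Greenhouse–Geisser (GG) multiplies both degrees of freedom by the estimated ε. At ε = 0.549 they become 3.8 and 438.

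**Result 1: false positives at nominal 5%**

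Eight samples, normal data, 10,000 runs per cell (simulation error about ±0.5 point).

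| Correlation pattern | ε | Uncorrected, 58 / 46 per arm | GG, 58 / 46 per arm |
|---|---|---|---|
| Constant 0.5 | 1.00 | 5.4% / 4.5% | 4.9% / 4.1% |
| AR(1) by visit order, 0.5 | 0.72 | 7.3% / 6.9% | 4.9% / 4.3% |
| AR(1) by visit order, 0.7 | 0.55 | 8.7% / 8.7% | 5.0% / 4.9% |
| AR(1) by visit order, 0.9 | 0.40 | 10.5% / 9.9% | 4.7% / 4.9% |
| Calendar decay, 30 days | 0.58 | 8.6% / 9.1% | 4.8% / 4.9% |
| Calendar decay, 90 days | 0.43 | 10.5% / 9.5% | 4.7% / 4.5% |
| Calendar decay, 180 days | 0.35 | 11.3% / 11.5% | 4.8% / 4.9% |
| Random intercept + 30-day decay + noise | 0.77 | 7.0% / 7.2% | 4.9% / 5.1% |
| Random intercept + 90-day decay + noise | 0.70 | 7.2% / 7.4% | 4.6% / 4.9% |

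- Seven samples (Table 1): 4.7–5.2% under constant correlation and 6.0–10.1% otherwise, uncorrected; 4.3–5.1% with GG.
- Four samples, as for TUG and 6MWT: 4.9–7.0% uncorrected, so the problem is smaller there.
- Unequal variances alone suffice. With constant correlation 0.5 and SDs in the ratio 1, 1, 2, 2, 1.5, 1, 1, 1, ε is 0.68. The uncorrected rate is then 7.3%, against 4.5% with GG.
- Lognormal data on the raw scale: 7.5–10.2% uncorrected, 3.0–5.4% with GG.
- Logging alone does not cure it. In a separate run (48 per arm, 3,000 runs per cell), log-scale uncorrected rates were 4.9–5.5% under constant correlation but 7.2–8.3% under decaying correlation.

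**Result 2: power with GG applied, raw against log scale**

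Eight samples, 58 per arm, true reduction at weeks 1, 4 and 8, AR(1) 0.7 or random intercept plus 30-day decay, 4,000 runs per cell.

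| Log SD | 20% reduction, raw | 20% reduction, log | 30% reduction, raw | 30% reduction, log |
|---|---|---|---|---|
| 0.3 | 99–100% | 100% | 100% | 100% |
| 0.6 | 38–44% | 55–69% | 82–90% | 97–99% |
| 0.8 | 18% | 29–37% | 41–48% | 73–87% |
| 1.0 | 9–10% | 19–24% | 19–22% | 49–64% |

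The separate run with 48 per arm and a 25% reduction from day 3 to week 8 gave 36–50% raw against 50–91% logged at log SD 0.8. At log SD 0.5, both scales exceeded 93%. The gain is not universal: one further case with fast-decaying correlation showed no advantage for the log scale.

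**The case against.** The strongest reply is that this reads silence as a decision. The article names repeated-measures ANOVA and stops. A sphericity correction is an option within that method, and the choice of scale is detail that an article often leaves to the full plan. This stands in part: a reader might infer that the article commits to untransformed data and an uncorrected F test, and it says neither. What remains is that Section 2.8.2 does address distributional assumptions, and its rules stop short of the analysis that carries the blood markers.

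Other objections, and what is left of them:

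- **Spacing.** A reader might blame uneven spacing itself. With time as a factor the ANOVA ignores spacing, and AR(1) by visit order alone gives about 7–10.5%. The cause is unequal variances of between-visit differences, which wide gaps make likely.
- **Doubling.** A reader might conclude that the error rate doubles. That is the upper part of a range running from no inflation to about 2.3-fold (11.5/5).
- **Skewness.** The article gives no SDs for D-dimer, TAT, PAI-1 or tPA. Its only hint is thrombomodulin at 3.1 ± 1.3 ng/mL with a range of 3 to 300 (Section 2.7.6). The power loss is conditional on that assumption.
- **Another route.** The normality check and Mann–Whitney rule are worded generally, and Mann–Whitney gives the same answer on raw and log values. It can compare arms at one visit, but it does not test whether change over time differs between arms.
- **Reach.** Lactate follows a perioperative schedule (Section 2.7.4) that these simulations do not represent. For albumin and prealbumin, no harm from the choice of scale is shown. Haemostasis is one of several unranked secondary objectives, not the leading one.

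**Conclusion.** The point holds in a limited form. Section 2.8.2 fixes one longitudinal method for serial markers and leaves it outside its own provisions for non-normal data.

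- **Error rate.** If the F test is run uncorrected, a nominal 5% arm-by-time test can become a 7–11% test with seven or eight samples. There is no inflation if sphericity happens to hold. With a Greenhouse–Geisser correction, the rate was 4.1–5.1% in every eight-sample normal-data case.
- **Power.** On strongly skewed markers (log SD about 0.6–0.8 or more), the raw scale can lose much of the power for a proportional effect even after that correction. At log SD of about 0.5 or less the loss is small.

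Both sizes rest on assumed correlations and skewness, which the article does not give. The documents do not support saying that error rates will double or that real effects will be hidden across all markers. The sample-size basis of the two primary comparisons, 3-day CAS and 6MWT at eight weeks, is not affected.

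**What to change.** 1. Replace the ANOVA sentence in Section 2.8.2 with a mixed model for every outcome with more than two time points: arm, categorical time and their interaction, with unstructured covariance. Eight visits mean 8 × 9/2 = 36 covariance parameters and seven mean 28, so name a fallback structure in case the model does not converge. The minimum alternative is to keep the ANOVA and specify a Greenhouse–Geisser correction.
2. Name in advance the haemostatic concentrations to be analysed on the log scale (for example D-dimer, TAT, PAI-1, tPA and thrombomodulin). Report arm effects as geometric mean ratios with 95% CI.
3. Reconcile Table 1 with Sections 2.7.5 and 2.7.6 on the sample one day before surgery, so that the number of time points in the model is fixed.

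The cost is wording only, with no new patients or samples. The one drawback is that effects on logged markers are read as ratios instead of differences.

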#### 2.7.7. Mortality and Incidence of Thrombotic/Thromboembolic Events

All thrombotic (e.g., myocardial infarction and stroke) and thromboembolic events (e.g., pulmonary embolism and deep vein thrombosis) will be recorded throughout the study. All-cause mortality will also be documented. Follow-up will take place up to 1 year after surgery.

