#### 2.7.9. Readmission Rate for Any Reason

All-cause readmission within 30 days after surgery will be recorded and at all other assessment time points (8, 26 and 52 weeks postoperatively).

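### Kaplan–Meier curves for readmission and thrombosis, read in the standard way with deaths censored, modestly overstate the proportion of patients who have these events by one year

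*Protocol article*

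**What the plan says.** Section 2.8.2 (Data Analysis) puts death, readmission and thrombosis in one list and gives all of them the same display: "the time to occurrence of an event (e.g., death, readmission to hospital, thrombosis, etc.) will be presented with a Kaplan–Meier survival curve". For factors related to these times, it says that "semiparametric (Cox proportional hazard models) or parametric survival analysis models (e.g., Weibull, exponential, etc.) will be performed". Competing risks, cumulative incidence and a composite with death are not mentioned, and no rule is given for a patient who dies before the event.

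Section 2.7.7 makes death an outcome in its own right, alongside thrombotic and thromboembolic events: "All-cause mortality will also be documented. Follow-up will take place up to 1 year after surgery". Section 2.7.9 covers readmission over the same year: "All-cause readmission within 30 days after surgery will be recorded and at all other assessment time points (8, 26 and 52 weeks postoperatively").

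On mortality, section 2.8.1 cites a Greek cohort in which "mortality at six months after a fracture is 10.5" per cent, and adds that "this particular study reports a lower incidence of mortality at 6 and 12 months postoperatively compared to studies in other countries". The Discussion lists mortality, rehospitalization and thrombotic or thromboembolic events among the secondary objectives.

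**The concern.** A patient who dies without having been readmitted can never be readmitted. Kaplan–Meier with deaths censored treats that patient as someone who could still have the event later, with the same hazard as those still under observation. One minus the curve then describes a setting in which nobody dies. Whenever some patients die event-free, it is larger than the proportion who have the event. The direction follows from the mathematics and needs no assumption.

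Mortality in this population is high enough for the gap to be visible, and the protocol enlarges its sample partly because of it. At stake are the one-year risks of readmission and thrombosis that readers would take from the curves. Their confidence intervals would not reveal a bias that always runs one way.

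**Working it through.** **Inputs from the protocol article.** Six-month mortality is 10.5% (2.8.1), the sample is 116 with 58 per arm (2.8.1), and follow-up is one year (2.7.7, 2.7.9).

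**Inputs that are assumptions.** The documents give neither one-year mortality nor any risk of readmission or thrombosis. I take Kaplan–Meier one-year event risks K of 10%, 20% and 30%, and one-year death risks D of 10.5%, 19.9% and, as an outer case, 30%. Hazards are constant and independent, so overall mortality can serve as the death hazard among patients who have not yet had the event.

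**Stated figures.** The plan has no readmission or thrombosis figure to reproduce. Its sample size does reproduce (96 × 1.2 = 115.2, taken to 116), but it does not bear on this point.

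**Mortality carried forward.** A constant hazard through the second half-year gives 1 − 0.895² = 0.199. In numbers, 116 × 0.105 is about 12 deaths by six months, and 116 × 0.199 is about 23 by one year.

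**Formulas.**
- Event hazard h = −ln(1 − K); death hazard d = −ln(1 − D).
- One minus Kaplan–Meier, deaths censored: 1 − exp(−h) = K.
- Cumulative incidence with death competing: [h/(h + d)] × [1 − exp(−(h + d))].

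**Worked case, K = 20%, D = 19.9%.** h = 0.2231 and d = 0.2219, so h/(h + d) = 0.5014. Also 1 − 0.80 × 0.801 = 0.3592. The cumulative incidence is 0.5014 × 0.3592 = 18.0%, against 20% from Kaplan–Meier: an excess of 2.0 points.

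| One-year death | K = 10% | K = 20% | K = 30% | Relative excess |
|---|---|---|---|---|
| 10.5% | 9.5% (+0.5) | 19.0% (+1.0) | 28.5% (+1.5) | about 5% |
| 19.9% | 9.0% (+1.0) | 18.0% (+2.0) | 27.1% (+2.9) | about 11% |
| 30% | 8.4% (+1.6) | 16.9% (+3.1) | 25.5% (+4.5) | about 18% |

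Cells show the cumulative incidence, with the Kaplan–Meier excess in points in brackets.

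**Early events.** With 70% of the event hazard in the first month and 19.9% one-year mortality, the excess falls to 0.4, 0.7 and 1.1 points. For a 30-day display it is below 0.3 points.

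**Rarer events.** At K = 5%, which might suit thrombosis, the excess is 0.3 points at 10.5% mortality and 0.5 points at 19.9%.

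**Comparison with sampling error.** The standard error per arm, √[K(1 − K)/58], is 3.9, 5.3 and 6.0 points for K = 10%, 20% and 30%.

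**The case against.** The strongest reply is that the article never says deaths will be censored. Event definitions and censoring rules are often left to an analysis plan, and readmission-free survival would avoid the problem. It is right that censoring at death is an inference. But death is a separate outcome, no composite is named, and a readmission or thrombosis curve by Kaplan–Meier is the stated method. Censoring at death is the ordinary way to draw it.

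Second, much of what is needed is already planned. A Cox model that censors at death gives a valid cause-specific hazard ratio. Section 2.8.2 also plans frequencies and a chi-square test for categorical variables. Applied to readmission as yes or no with otherwise complete follow-up, that percentage keeps the deaths in the denominator. This stands, and it confines the fault to the curves when they are read as absolute risks.

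Third, section 2.7.7 does not restrict thrombotic events to non-fatal ones, so a fatal infarction, stroke or pulmonary embolism is itself the event and not a competing death. This stands too and is built into the fix.

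Two stronger readings are tempting, and the documents support neither:
- **A much larger bias.** A reader might infer up to 6.5 points by placing all deaths early. That needs 25% of patients dead within three months, against the protocol's 10.5% at six. The eligibility criteria (2.4.1, 2.4.2) also exclude some of the frailest patients, so trial mortality could be lower still.
- **A distorted comparison between arms.** Suppose the readmission hazards are equal (K = 30%) and deaths are 10% v 20%. The cumulative incidences are then 28.6% v 27.1%, while Kaplan–Meier shows 30% in both arms. As a comparison of hazards, Kaplan–Meier is right here, and the lower incidence belongs to the arm with more deaths. The 1.5-point gap is also small beside a standard error of about 8.3 points for the difference. Either display needs mortality beside it.

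**Conclusion.** The point holds as a minor one. Under the standard reading, the stated display overstates the one-year proportion with readmission or thrombosis. The excess is about 0.5–1.5 points if one-year mortality is 10.5%, and 1.0–2.9 points if the six-month hazard persists to 19.9%. These ranges assume constant independent hazards and Kaplan–Meier risks of 10–30%, and they shrink if events cluster early.

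The bias is smaller than one standard error per arm, but it always goes in the same direction. It affects the displayed absolute risks of secondary outcomes only. The primary outcomes, the sample size, the Kaplan–Meier curve for death and the Cox hazard ratios, read as cause-specific, are untouched.

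**What to change.** In section 2.8.2:
- Keep Kaplan–Meier for all-cause death.
- For readmission and for thrombotic or thromboembolic events, show Aalen–Johansen cumulative incidence by arm. Death without a prior event is the competing event, and a fatal thrombotic event counts as the event.
- Label the Cox results for these outcomes as cause-specific, and report them beside the hazard ratio for death.

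The cost is a sentence or two of analysis wording and a little programming. Deaths are already recorded under section 2.7.7, so no data, visits or patients are added. The downside is slightly lower displayed risks and one extra line of explanation for readers. Settling this before the analysis also avoids a choice made after seeing the results.
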